### Intervention

Eligible participants will be randomized to the intervention (i.e., immediate access to the 14-day self-paced online training period) or to a wait-list control group (i.e., 14-day delay before online training access) following a 1:1 ratio using a random number generation procedure implemented in Microsoft Excel. Participants will be blinded as per the different conditions. The intervention will consist of an on-demand online training which will be implemented in a Moodle learning management system to ensure better integration into the everyday work of clinicians through easy accessibility and self-paced learning. Such formats are common in the field [22] and follow recommendations for engaging online trainings [23,24]. For reasons of compatibility with everyday working life, we also deliberately opted for short, separate modules after carefully weighing up the advantages and disadvantages. The six modules are presented as learning videos with presentation slides, demonstrational dialogues, reflexive exercises and supporting downloadable in-depth resources, and should be completed online in 5–10 minutes each (corresponding to a total duration of 45–50 minutes), followed by interactive questions, ratings and quizzes. The module structure and corresponding contents are summarized in Table 1.

**Table 1 pone.0333997.t001:** iSMEsH Online Training Intervention Modules and Content.

Module #	Title	Content
1	Introduction to Eating Disorders	• Diagnostic criteria, clinical impressions and epidemiology of EDs in Boys and Men • Etiological Concepts • Promoting sensitivity to diversity • Implications of stigmatization as “second illness”
2	Symptoms and Diagnostics	• Clinical signs for suspected EDs on the psychological, social and physical level • Guiding questions for psychological and physical examination • Standardized diagnostic instruments (questionnaires, interviews) • Basic principles of somatic co-treatment • (Compulsive) hospital referral and stepped care
3	Communication Skills	• Recommendations for inclusive and non-discriminatory communication • Directly addressing stigma with patients • Basic principles and concepts of Motivational Interviewing • Perspective-taking exercise

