### Participant timeline

Individuals interested in taking part in the study can self-enroll via a webform on the project website (https://maennermitessstoerung.rub.de), which is referenced as link and QR code in leaflets and mailings. At enrollment (-t_1_), participants will answer baseline and sociodemographic questions, undergo eligibility assessment and be allocated to their respective participant group (GP or medical student) and study arm (intervention or wait-list control). Participants allocated to the wait-list control groups will be informed that they need to wait 14 days for the online training. Participants of the wait-list control groups will be meanwhile invited to a quantitative pre-participation assessment at t_1_ within the two-week waiting period, after which they will receive the personalized login credentials for the online learning platform to administer a quantitative pre-intervention assessment at t_2_ (end of the waiting period), then followed by the actual online training and a quantitative post-intervention assessment at t_3_. By contrast, participants allocated to the intervention group directly receive personalized login credentials for the learning platform at t_1_ (enrollment) and administer pre-intervention assessments before participating in the online training, followed by a quantitative post-intervention assessment at t_2_. Intervention group participants will be contacted to administer a quantitative post-participation/follow-up assessment at t_3_ another 14 days after they have completed the online training. Both groups will have 14 days to complete the training. To minimize the risk of participant dropout, participants will receive reminder emails on several time points during their participation (a reminder for completing the pre-survey 1 week after receiving the pre-survey link, a reminder for completing the online training one week after receiving login credentials and another reminder two days before termination of the 14-days participation time window, and a reminder for the post-survey 1 week after receiving the post-survey link). This procedure applies to both GPs and medical students allocated to the respective study arms. Finally, selected participants of the GP groups are invited to a qualitative telephone interview (t_4_) about four months after completion of the online training and respective quantitative assessments (see Fig 2).

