### Assignment of interventions

Participants will be randomly assigned to either the control or intervention conditions with a 1:1 allocation as per a specified randomization schedule. Randomization will be conducted electronically. Blinding of the researcher conducting the interviews was deemed infeasible, but participants will be blinded as per the different study conditions.

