### Data collection methods

All quantitative and qualitative data will be collected pseudonymously via electronic data capture tools (see below). Regarding primary outcomes, the cognitive facet of stigma (i.e., stereotypes) will be operationalized in terms of knowledge deficits regarding EDs in boys and men. We will construct and pilot a set of ten single-choice items (with five alternative answers each, from which one correct answer must be selected). The items will be collaboratively constructed based on literature search and intensive discussions within our team of experienced scientists and clinicians and the lived experience advisory board members. The global score will be calculated as the sum of correct answers over all items. The affective facet of stigma (i.e., prejudice) will be assessed using an adapted version of the validated German [25] Opening Minds Stigma Scale for Health Care Providers (OMS-HC) [26] replacing “person with a mental illness” with “men with an eating disorder”. The OMS-HC includes 15 self-report items rated on a 5-point Likert scale from 1 (*strongly disagree*) to 5 (*strongly agree*). The attitudes subscale score will serve as the primary dependent variable regarding the affective stigma facet. The behavioral facet of stigma will be assessed with three adapted items of the German version [34] of the General Self-Efficacy Scale (GSE) [27] (“I can remain calm when facing difficulties in the treatment of men with eating disorders because I can rely on my coping abilities”, “I am confident that I could deal efficiently with unexpected events in the treatment of men with eating disorders”, “When I am confronted with a man with an eating disorder, I can usually find several solutions”). Responses are made on a 4-point scale ranging from 1 (*not at all true*) to 4 (*exactly true*). An overall score will be computed as the sum of the three items.

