#### Consent.

Participants of both the advisory board and the actual online training intervention throughout the different phases are informed and educated about the procedure and study goals prior to data collection (for consent forms and written study information, see **Supplement**). Written informed consent, as defined by the Declaration of Helsinki, is a prerequisite for study participation and will be obtained from all participants prior to their enrollment. All participants will receive a copy of their submitted consent forms at their disposal.

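### The protocol twice calls participants blinded, but under its own timeline they know whether they have been trained when they rate themselves at t2

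*Protocol article*

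**What the plan says.** Two sections of the protocol article claim participant blinding. Intervention: "Participants will be blinded as per the different conditions". Assignment of interventions first concedes that the interviewer cannot be blinded and then adds: "but participants will be blinded as per the different study conditions". Masking of participants is thus put forward as a property the trial has.

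The arms differ only in when access to the course is given. The control is described as a "wait-list control group (i.e., 14-day delay before online training access", and no sham course or attention control is mentioned. The Participant timeline says what each arm is told or given after allocation. For the control arm: "Participants allocated to the wait-list control groups will be informed that they need to wait 14 days for the online training". For the other: "participants allocated to the intervention group directly receive personalized login credentials for the learning platform". The Consent section adds that participants "are informed and educated about the procedure and study goals prior to data collection".

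On measurement, Data collection methods states: "The OMS-HC includes 15 self-report items rated on a 5-point Likert scale". Its attitudes subscale is the primary measure of the affective facet. The behavioural facet is three adapted self-efficacy items, self-rated on a 4-point scale. The secondary outcome is seven perception items, also self-rated. The cognitive facet is a count of correct answers to ten single-choice questions.

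Strengths and limitations names reliance on self-report, but in connection with generalisability. It does not mention blinding.

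**The concern.** Blinding of participants means that they do not know which condition they are in. Here the condition is whether the course has been opened to them yet, and the protocol tells them that directly. The two statements therefore claim a property that the described procedure does not provide.

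This bears on how the results can be read. The course teaches about stigma and non-discriminatory communication, so someone who has just completed it can see which answers on an attitude or self-efficacy scale are the desirable ones, and may also expect to have improved. Someone still waiting has had no such exposure, and may be affected by the wait itself. A between-arm difference in self-ratings can then mix real change with a change in how people answer. A results paper or a risk-of-bias assessment that took the two blinding statements at face value would set this aside when it should be weighed.

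**Working it through.** The point rests on comparing passages. The protocol gives no figure for blinding, so there is none to reproduce.

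1. **What is claimed.** Intervention and Assignment of interventions both say participants are blinded with respect to the conditions. Neither says what is withheld from them.

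2. **What distinguishes the conditions.** Immediate access against a 14-day delay. With no sham or attention control, the arms have no shared experience that could mask the difference.

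3. **What participants learn, and when.** At enrolment they are allocated. Wait-list participants are told of the wait; intervention participants receive their credentials.

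4. **State of each arm at the three quantitative assessments** (Participant timeline):

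| Assessment | Intervention arm | Wait-list arm |
|---|---|---|
| t1 | untrained, has login | untrained, told to wait |
| t2 | trained | untrained, wait just ending |
| t3 | trained, follow-up | trained |

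The arms differ in training status only at t2. That is where knowledge of one's own status can bias a trained-versus-untrained comparison. By t3 both arms have been trained.

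5. **Which outcomes are exposed at t2.**
   - OMS-HC attitudes (primary, affective): self-rating, exposed.
   - Adapted self-efficacy items (primary, behavioural): self-rating, exposed.
   - Perception scale (secondary): self-rating, exposed.
   - Knowledge test (primary, cognitive): completed by the participant but scored against one correct answer in five, so less exposed.

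   That is two of the three stigma primary outcomes plus the secondary outcome.

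6. **What is not affected.** The stated sample size was checked for context. With f = 0.15, r = 0.50, ε = 1, α = 0.05, k = 2 groups and m = 3 times, λ = f²·N·m/(1 − r), df1 = (k − 1)(m − 1) = 2 and df2 = (N − k)(m − 1). At N = 74, λ = 0.0225 × 74 × 3/0.5 = 9.99, df2 = 144 and power is 0.806. The smallest N reaching 0.80 is 73 (power 0.801), which becomes 74 with equal groups. The protocol's 74 is reproduced, and correcting the blinding statements changes none of it.

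7. **Can the bias be sized?** Not from this document. A share of the planned effect would need two things that it does not give. The first is the shift in self-ratings caused by knowing one's status. The second is the t2 difference implied by f = 0.15, which depends on an effect pattern the protocol does not state.
   - If arm differences at t1, t2, t3 are 0, d, 0, the standard deviation of the interaction effects is d/√18, so d = 0.15 × 4.243 = 0.64 SD.
   - If half the effect fades in the intervention arm by t3, the differences are 0, d, −d/2 and d is about 0.48 SD.
   - An assumed shift of 0.1 to 0.3 SD would be 16 to 47% of the first figure and about 21 to 62% of the second.

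   The spread shows that the percentages come from the assumptions and not from the trial's own figures, so none is put forward as a result.

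**The case against.** The strongest defence is a narrower meaning of the two sentences: participants may simply not be told that a second, differently timed arm exists. The timeline says only that wait-list participants hear of their own delay, not that they hear of a comparison arm. The consent forms are in a supplement that is not shown, so this reading cannot be excluded. The Consent section, under which participants are told about procedure and goals beforehand, points against it. Even if it is right, people still know at t2 whether they have taken the course, and that knowledge is what matters for self-ratings. What stands is that the intended meaning is uncertain and must be spelled out.

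It is also fair to say that little is concealed. The wait-list design is described openly, and reliance on self-report is listed as a limitation in both the Abstract and Strengths and limitations. What is missing is the link between self-rating and lack of blinding, as a question of internal validity.

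A reader might infer more than the documents support:

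- *That the trial is simply open-label.* The protocol never uses the term, and the narrower reading above remains possible.
- *That bias acts on the trained arm only.* This describes the t2 comparison at most. Both arms are trained by t3, and being made to wait could itself move the control arm's ratings.
- *That this is the trial's main bias.* Nothing in the document ranks it against other sources of bias.
- *That the analyst should be masked, or that conclusions should lead with the knowledge test.* Analyst masking does nothing for participants' expectations. The protocol sets knowledge, attitudes and self-efficacy side by side, and reordering them is a preference that does not follow from this contradiction.

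**Conclusion.** The point holds as an error of description with a consequence for interpretation. The blinding statements in Intervention and Assignment of interventions cannot stand beside the Participant timeline on the ordinary meaning of the word. On the narrower meaning they are undefined and still leave participants aware of their training status at t2.

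The consequence is limited to risk of bias in the t2 between-arm comparison for attitudes, self-efficacy and perceptions. It is smaller for knowledge. It is not a fault in sample size, allocation or models. Its magnitude is unknown and cannot be derived from the document.

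The conclusion rests on two things: that the timeline describes what participants will actually be told, and that the absence of any described sham or attention control means there is none. It should be corrected, because the remedy is cheap and it governs how three of the four stigma-related outcome measures may be read.

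**What to change.** 1. In Intervention and in Assignment of interventions, replace the blinding sentences with one consistent statement: *participants are not blinded to whether and when they receive the training*. If only the existence of the other arm is concealed, say exactly that, and say that participants still know their own training status.
2. Check that this statement agrees with the Participant timeline and with the information given at consent.
3. In Strengths and limitations, add lack of participant blinding combined with self-rated outcomes as a limitation of internal validity, separate from the existing remark on generalisability.
4. Carry the caveat into the results paper, so that t2 effects on attitudes, self-efficacy and perceptions are described as open to expectation and social-desirability bias.

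The cost is wording only. Recruitment began in July 2024, but nothing in conduct, randomisation, sample size or analysis has to change. The one downside is that the reported risk of bias will look less favourable.

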### Outcomes

The primary outcomes include the cognitive, affective and behavioral facets of ED-associated stigma and implementation quality. The cognitive aspects will be assessed with ten collaboratively developed single-choice questions to assess knowledge on EDs in boys and men; affective aspects will be assessed using the German version [25] of the Opening Minds Stigma Scale for Health Care Providers (OMS-HC) [26]; behavioral aspects will be assessed using the General Self-Efficacy Scale (GSE) [27]. Following Proctor et al. [20], implementation quality will be assessed along the dimensions of acceptability, feasibility, appropriateness, and adoption with self-developed rating questions; fidelity, penetration and sustainability will be assessed in a semi-structured interview by means of open-ended questions.

The secondary outcome includes stigma-related perceptions of EDs in men (Lehe et al., 2024).

Additional baseline variables considered potential covariates include sociodemographic features via the Diversity Minimal Item Set (DiMIS) [28] and self-developed items, study and job characteristics, professional medical background, professional attitude towards mental health, personal experiences with mental disorders and impairments, professional experiences with patients with EDs. We will additionally assess participants’ self-perceived identification with masculine and feminine gender roles at baseline through the Traditional Masculinity-Femininity Scale (TMF) [29] to assess potential moderating effects of gender role endorsement regarding anti-stigma effects.

### Participant timeline

Individuals interested in taking part in the study can self-enroll via a webform on the project website (https://maennermitessstoerung.rub.de), which is referenced as link and QR code in leaflets and mailings. At enrollment (-t_1_), participants will answer baseline and sociodemographic questions, undergo eligibility assessment and be allocated to their respective participant group (GP or medical student) and study arm (intervention or wait-list control). Participants allocated to the wait-list control groups will be informed that they need to wait 14 days for the online training. Participants of the wait-list control groups will be meanwhile invited to a quantitative pre-participation assessment at t_1_ within the two-week waiting period, after which they will receive the personalized login credentials for the online learning platform to administer a quantitative pre-intervention assessment at t_2_ (end of the waiting period), then followed by the actual online training and a quantitative post-intervention assessment at t_3_. By contrast, participants allocated to the intervention group directly receive personalized login credentials for the learning platform at t_1_ (enrollment) and administer pre-intervention assessments before participating in the online training, followed by a quantitative post-intervention assessment at t_2_. Intervention group participants will be contacted to administer a quantitative post-participation/follow-up assessment at t_3_ another 14 days after they have completed the online training. Both groups will have 14 days to complete the training. To minimize the risk of participant dropout, participants will receive reminder emails on several time points during their participation (a reminder for completing the pre-survey 1 week after receiving the pre-survey link, a reminder for completing the online training one week after receiving login credentials and another reminder two days before termination of the 14-days participation time window, and a reminder for the post-survey 1 week after receiving the post-survey link). This procedure applies to both GPs and medical students allocated to the respective study arms. Finally, selected participants of the GP groups are invited to a qualitative telephone interview (t_4_) about four months after completion of the online training and respective quantitative assessments (see Fig 2).

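### The first outcome measurement (t1) follows allocation in both arms and has no fixed day in the wait-list arm, so the group-by-time effect rests on a reference point that allocation could influence

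*Protocol article*

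**What the plan says.** All of the following is in the protocol article.

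**Sequence.** Participant timeline gives the enrolment steps as: "At enrollment (-t_1_), participants will answer baseline and sociodemographic questions, undergo eligibility assessment and be allocated to their respective participant group". The arm is assigned in the same step. Next: "Participants allocated to the wait-list control groups will be informed that they need to wait 14 days for the online training". Those participants are then "invited to a quantitative pre-participation assessment at t_1_ within the two-week waiting period", and their t2 is the "pre-intervention assessment at t_2_ (end of the waiting period"). In the other arm, "participants allocated to the intervention group directly receive personalized login credentials for the learning platform at t_1_ (enrollment"). For this arm t1 is placed ahead of the course, since these participants "administer pre-intervention assessments before participating in the online training". The section also provides for "a reminder for completing the pre-survey 1 week after receiving the pre-survey link".

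**What is collected before allocation.** Outcomes and Data collection methods list the baseline variables as sociodemographic and job data, attitudes to mental health, personal and professional experience, and the TMF. The knowledge items, OMS-HC and self-efficacy items are not among them.

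**Blinding.** Intervention and Assignment of interventions both state that participants are blinded to condition.

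**Use of t1.** Data analysis makes t1 one of three time points in the 2 x 3 ANOVA (per protocol, case-wise exclusion) and in the mixed model (intention to treat, with and without multiple imputation). The interaction contrast has six non-zero coefficients, so both t1 cells carry weight in it.

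**The concern.** In a wait-list trial the pre-training measurement should be unaffected by allocation, because change is judged against it. Here t1 is the only untrained outcome measurement that both arms share, and it comes after allocation. Three things could make it differ by arm.

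1. **Reaction to allocation.** Two of the three stigma outcomes are self-report scales (attitudes and self-efficacy). A participant who has just been told to wait may answer differently from one who has just been given access.
2. **Loss between allocation and t1.** If more people leave in one arm, those who supply t1 are no longer the randomised groups.
3. **Unequal retest intervals.** The same ten knowledge items and the same scales are repeated after intervals that vary within each arm and may differ between arms.

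An arm difference at t1 from any of these sources enters the group-by-time effect directly. It could mimic a training effect or hide one.

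**Working it through.** **1. Order of events, side by side**

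| Step | Intervention arm | Wait-list arm |
|---|---|---|
| Enrolment (−t1) | covariates, eligibility, allocation | covariates, eligibility, allocation |
| What the participant then learns | receives platform access | is told of a 14-day wait |
| t1 outcomes | after access, before training; no fixed day | by invitation during the wait; no fixed day |
| t2 outcomes | after training, which has a 14-day window | end of the wait |

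Allocation precedes t1 in both columns. In the wait-list arm, t1 can fall from the first to the last day of the wait, so t1–t2 can run from about 14 days down to about 0. A participant who answers only after the one-week reminder has at most 14 − 7 = 7 days left, even if the link was sent at once. In the intervention arm, the course takes 45–50 minutes inside a 14-day window, so that interval floats as well.

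**2. Who enters which analysis**

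- Missing t1 only: dropped from the ANOVA by case-wise exclusion, but kept in the mixed model through t2 or t3.
- Missing t1 and everything after: adds nothing to the unimputed mixed model, and can enter only by imputation from the enrolment covariates.

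**3. The plan's own sample size**

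Inputs (Sample size): f = 0.15, r = .50, ε = 1, α = .05, power .80, 2 groups, 3 time points.

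λ = f² × N × m × ε / (1 − r) = 0.0225 × 74 × 3 × 1 / 0.50 = 9.99, with df = 2 and (74 − 2) × 2 = 144.

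Power is 0.806 at N = 74 and 0.795 at N = 72, so the stated 74 reproduces. At the planned 100 GPs, power is 0.914.

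**4. Illustration of a shifted t1**

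Assumption, not in the documents: wait-list t1 is shifted by s SD, every other cell mean is equal, and training has no effect.

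- The arm difference over time is (s, 0, 0). Centred over time it is (2s/3, −s/3, −s/3), with sum of squares 6s²/9.
- Half of each value goes to each arm with opposite sign, so the interaction sum of squares over the six cells is 2 × ¼ × 6s²/9 = s²/3.
- λ = (N/2) × (s²/3) / (1 − 0.50) = N s²/3.

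| s (assumed) | λ at N = 74 | Rejection rate, N = 74 | Rejection rate, N = 100 |
|---|---|---|---|
| 0 | 0 | 0.050 | 0.050 |
| 0.1 | 74 × 0.01/3 = 0.25 | 0.069 | 0.076 |
| 0.2 | 74 × 0.04/3 = 0.99 | 0.130 | 0.161 |

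**5. Scale against the planned effect**

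The protocol gives f, not a standardised difference. If the arms differ at t2 only, by d SD, the same algebra gives λ = N d²/3. Setting this equal to 6 f² N gives d = f × √18 = 0.15 × 4.243 = 0.64. On that assumed pattern, a shift of 0.1 to 0.2 SD is 0.1/0.64 = 16% to 0.2/0.64 = 31% of the planned effect. These percentages only rescale the assumed shift and are not evidence that it occurs.

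**The case against.** **No bias is shown.** Neither arm has been trained before t1, so the intervention does not contaminate it. The protocol does not say that anyone is told the wait is a control condition, and it is not obvious why news of a two-week wait would move a knowledge score. This stands. A reader might infer that the arms are not comparable at t1 or that randomisation is broken. The documents do not support that: they show that t1 is exposed to influence after allocation, not that it was influenced. The arms can also still be compared at t2, when only one has been trained.

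**Early leavers are not shut out.** A reader might infer that people who leave on hearing of the wait are lost to every intention-to-treat analysis. Data analysis plans imputation in case of dropout, and enrolment covariates exist to support it. That inference fails. What remains is that such people contribute no observed outcome.

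**Timing floats in both arms.** True. The unfixed interval is not peculiar to the wait-list arm. What is peculiar to it is the explicit notice of the wait before t1.

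**Unseen material.** Figure 2 (the assessment schedule) and the participant information are not shown. If the figure places the outcome scales before allocation, the point weakens. The visible text does not place them there. It does use the word enrolment for both −t1 and the intervention arm's t1, which itself needs clearing up.

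**It is late.** Recruitment began on July 23, 2024 and was expected to end by November 1, 2025, so changing the order helps only people still to be enrolled. This stands and limits the first part of the fix.

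**Conclusion.** The point holds as a design weakness. On the text, the first measurement of the three stigma outcomes follows allocation in both arms. In the wait-list arm it also follows notice of a 14-day wait and may fall on any day of that wait. This sits badly with the statements that participants are blinded to condition.

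Because t1 is a modelled time point in every between-arm analysis, an arm-dependent disturbance of t1 would carry into the group-by-time effect. The paired pre-post test is less exposed: the wait-list arm's pre-training value there is t2, and the test compares no arms.

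The size is unknown. The rise in false-positive rate from 0.05 to about 0.07 to 0.13 at N = 74 rests on an assumed 0.1 to 0.2 SD shift, r = .50, sphericity and no training effect. It shows sensitivity and is not an estimate. The sample-size arithmetic is unaffected. The matter should be corrected where possible and otherwise reported; it does not invalidate the trial.

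**What to change.** **Participants not yet enrolled.** Put the knowledge, OMS-HC and self-efficacy scales in the existing enrolment webform, after consent and eligibility, and release the allocation only on submission, in both arms. This costs a short amendment and a longer form, with some drop-off moved to before randomisation. It also leaves two t1 procedures in one dataset, so flag them with an enrolment-period indicator. The required N stays at 74, because f, r, ε and α do not change.

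**Participants already enrolled.**
- From survey time stamps, report by arm the lag from allocation to t1 and the t1–t2 interval.
- Report by arm the number randomised without t1, separating those with a later outcome from those with none.
- Add a sensitivity analysis comparing the arms at t2 without t1, adjusted for covariates collected before allocation. At r = .50 the variance of t1–t2 change is 2σ²(1 − .50) = σ², the same as that of t2 alone, so this loses no precision against a simple change comparison. It still depends on who supplies t2.

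**Text.** Reconcile the blinding statements in Intervention and Assignment of interventions with Participant timeline by saying what each arm is told and when. Use one label for enrolment and one for t1.

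The reporting and text items cost only analyst time and are possible at any stage.
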